## Abstract

**Background:** Pre-exposure prophylaxis (PrEP) is the use of HIV anti-retroviral therapy to prevent HIV transmission in people at high risk of HIV acquisition. PrEP is highly efficacious when taken either daily, or in an on-demand schedule. In Australia co-formulated tenofovir-emtricitabine is registered for daily use for PrEP, however, this co-formulation is not listed yet on the national subsidized medicines list. We describe a study protocol that aims to demonstrate if the provision of PrEP to up to 3800 individuals at risk of HIV in Victoria, Australia reduces HIV incidence locally by 25% generally and 30% among GBM.

**Methods:** PrEPX is a population level intervention study in Victoria, Australia in which generic PrEP will be delivered to 3800 individuals for up to 36 months. Study eligibility is consistent with the recently updated 2017 Australian PrEP guidelines. Participants will attend study clinics, shared care clinics, or outreach clinics for quarterly HIV/STI screening, biannual renal function tests and other clinical care as required. Study visits and STI diagnoses will be recorded electronically through the ACCESS surveillance system. At each study visit participants will be invited to complete behavioral surveys that collect demographics and sexual risk data. Diagnosis and behavioral data will be compared between PrEPX participants and other individuals testing within the ACCESS surveillance system. A subset of participants will complete in depth surveys and interviews to collect attitudes, beliefs and acceptability data. Participating clinics will provide clinic level data on implementation and management of PrEPX participants. The population level impact on HIV incidence will be assessed using Victorian HIV notification data.

**Discussion:** This study will collect evidence on the real world impact of delivery of PrEP to 3800 individuals at risk of acquiring HIV in Victoria. This study will provide important information for the broader implementation of PrEP planning upon listing of the tenofovir-emtricitabine on the national subsidized list of medicines. The study is registered on the Australian New Zealand Clinical Trials Registry (ACTRN12616001215415)

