PrEPX planning	Sep-Dec 2015	Approached clinics and community pharmacies to participate in the PrEPX study. Approached peak organizations including VAC, LPV, VACCHO, Centre for Culture, Ethnicity and Health.
	29 Jan 2016	Funding announced by the Victorian DHHS, Alfred Health and VAC for 2,600 places in PrEPX study.
	30 Jan 2016	Study registration opened using REDCap on the Alfred hospital website. Data collected: name, contact details, preferred clinic to attend for PrEPX, whether participant was on PrEP.
	22 Jul 2016	2049 people registered interest on online formClinics provided with partially de-identified list from registration form to enable workforce planning when study openedRegistered individuals emailed about study opening dates and booking information for their preferred clinic.
PrEPX study period	26 Jul 2016	PrEPX enrolment began (wave one of study enrolment) 2600 places opened, 150 of these reserved for priority populations including people who inject drugs and/or people in serodiscordant heterosexual partnerships with high or medium risk for HIV acquisition as per PrEP prescribing guidelines (Table 2).
	14 Oct 2016	PrEPX study neared enrolment capacityStudy enrolment stopped at 2200 participants to allow for people who had booked an appointment and not yet attended to join the study, with other places reserved for priority populations.First waitlist was opened, pending further funding.
	17 Jan 2017	Additional 600 places in PrEPX announced, funded by VAC.
	19 Jan 2017	Additional places released (wave two of study enrolment)All 575 people registered on the waitlist were provided a study place. Clinics were provided a list of participants as per original PrEP enrolment.
	20 Jan 2017	Waitlist was reopened.
	28 Mar 2017	Additional 600 places announced, funded by Victorian DHHS.
	29 Mar 2017	Additional places released (wave three study enrolment)All 617 people registered on the waitlist were provided a study place Clinics were provided list of participants as per original PrEP enrolment.
	30 Mar 2017	Waitlist was reopenedWaitlist remains open November 27th 2017.
	30 June 2019	PrEP-X study estimated end date.

*VicPrEP, Victorian PrEP demonstration study; PrEPX, Victorian PrEP population level study; PrEPX-SA, expansion of PrEPX study to South Australia; VAC, Victorian AIDS Council, LPV, Living Positive Victoria; VACCHO, Victorian Aboriginal Community Controlled Health Organisation Inc.; DHHS, Department of Health and Human Services*.

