### Study setting

The study is set in Victoria, the second most populous Australian state with a population of 6.2 million people and about 45,000 GBM (2, 39). In 2015, there were 286 new HIV diagnoses in Victoria of which 148 were defined as newly acquired [evidence of diagnosis within 12 months of infection (40)], with diagnosis rates of 4.8 and 2.0 per 100,000 population, respectively (1). In metropolitan Melbourne (the capital of Victoria), where approximately 80% of people newly diagnosed with HIV in Victoria reside (41), PLWH and GBM are cared for by three types of clinics: a small number of general practice clinics that have high caseloads of PLWH and GBM, state-funded sexual health services, and infectious disease (ID) clinics at teaching hospitals. The Alfred Hospital provides a state wide HIV service. These three types of clinics are staffed by general practitioners, sexual health clinicians and infectious disease clinicians who are licensed to prescribe antiretroviral medications on the PBS. Since 2013, the PBS has provided ARVs to PLWH at any CD4 cell count (previously restricted to a CD4 cell count below 500 cells/ml). PrEPX study sites include GBM specialist GP clinics, state-funded sexual health service, the Alfred hospital HIV service, shared care and outreach study sites (Table 1).

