### Data collection

#### Registration and waitlist data collection

When study funding was announced in January 2016, a database (study registry) was established so that individuals could register their interest in the study thereby assisting the study team's plans for study implementation (Table 1). The register collects participants' contact details, previous PrEP use and which study site participants would prefer to attend.

A few days prior to commencement of study enrolment, registered individuals were emailed information on how to book a PrEPX appointment at their preferred study site and information on whether co-payment would likely be required by the clinic at study enrolment. Clinics were provided with a list of individuals planning to attend their clinic, including contact details, if currently using PrEP and if currently a client at that clinic.

The study opened on 26 July 2016 and data collection among enrolled participants is scheduled until July 2019.

As enrolment neared capacity (*n* = 2,600) a waitlist register was established so individuals could register their interest if further places became available. The waitlist register collected the same variables as the initial registry of interest. Consistent with the protocol at study opening, with each release of additional study places registered individuals were emailed details of their preferred study site and clinics were emailed information on their potential PrEPX participants.

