#### Other study data

Clinic staff at three of the four Victorian primary care clinics, two sexual health clinics, and the hospital clinic have been invited to complete a survey about characteristics of their clinic, their PrEP patient load and clinic level challenges experienced during the study at baseline, months 12 and 24.

Pharmacy data including drug accountability logs and participant record logs are manually collected from each participating site.

Victorian HIV diagnosis data will be collected from the Victorian Department of Health and Human Services (DHHS). It is a legal requirement that all newly diagnosed cases of HIV are notified to the DHHS. Notifications include test result data from the laboratory and an enhanced surveillance form from the diagnosing doctor that includes demographics, test history and exposure to HIV. Non-identifiable line listed data will be collected from the Victorian DHHS including the diagnosis date, country of birth, age, and exposure to HIV for all newly diagnosed cases in Victoria between 2013-2019.

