### Statistical analyses

The study will determine if the provision of PrEP to 2,600 people at high risk of HIV infection in Victoria results in a 30% decline in new HIV infections among GBM over the 36 months of the study. In addition, the study will monitor the rate of new HIV infections in Victoria for a period of 36 months after the PrEPX study commences. Analyses of changes in the rates of HIV infection will be undertaken using Mann-Whitney U and chi-square tests to determine whether there has been a significant decline in new HIV infections during this 36-month period, compared to the 36 months prior to PrEPX commencing.

We will undertake further analyses to determine whether or not other factors such as an increase in background HIV and STI testing rates during the PrEPX study period and an increase in the background rate of HIV virological suppression of HIV positive people living in Victoria during the PrEPX study period may have contributed to any decrease in new HIV infections. These analyses will be undertaken using Cox proportional and logistic regression analyses to calculate hazard or rate ratios and odds ratios, respectively, with 95% confidence intervals. To determine the factors associated with incident HIV infection among trial participants, we will explore demographic and behavioral risk factors.

To answer the study secondary aims a range of datasets and analyses will be employed, as required. The enrolment survey, ACCESS behavioral survey, and ACCESS test data will be used to explore baseline demographics, behavior, HIV risk factors, prevalence of STIs and blood borne viruses among GBM presenting for PrEP, changes in behavior and STI rates among PrEP users and ancillary health benefits among PrEP users. The in-depth online survey and interviews will be used to explore attitudes to PrEP, reasons for taking PrEP and attitudes around sexual behavior since the availability of PrEP. We will use ACCESS test data, pharmacy data and in-depth online surveys to explore PrEP adherence. Monthly aggregate data from the state NPEP service will be descriptively analyzed to explore state wide use of clinic survey and ACCESS test data will be used to explore the capacity of study clinics to prescribe PrEP.

All statistical analyses will be performed using Stata version 14 (StataCorp LP, College Station, Texas, USA) with a significance cut off of *p* = 0.05.

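### With no lag after the first day of enrolment, the 36 v 36 month comparison of notifications understates the decline to be judged against the 30% and 25% targets

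*Protocol article*

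**What the plan says.** The Abstract names the data source: "The population level impact on HIV incidence will be assessed using Victorian HIV notification data". Under Other study data, the line list from the state health department is non-identifiable, covers 2013 to 2019 and holds fields "including the diagnosis date, country of birth, age, and exposure to HIV". The date available for each case is thus the date of diagnosis.

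Statistical analyses fixes the windows. The study will "monitor the rate of new HIV infections in Victoria for a period of 36 months after the PrEPX study commences", and the test looks for a significant decline "during this 36-month period, compared to the 36 months prior to PrEPX commencing". On the starting date the data collection section says: "The study opened on 26 July 2016 and data collection among enrolled participants is scheduled until July 2019". Table 1 gives the same day for the first enrolment. The two windows therefore meet on the day recruitment began. The article states no lag, washout or transition period.

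Study setting defines newly acquired cases by "evidence of diagnosis within 12 months of infection"; 148 of the 286 diagnoses in 2015 met that definition. Statistical analyses also plans to examine background testing and viral suppression as factors that "may have contributed to any decrease in new HIV infections". The Discussion concedes that diagnoses are only a proxy for incidence and proposes to triangulate notifications with ACCESS data. It does not alter the windows.

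**The concern.** A diagnosis made in August 2016 usually reflects an infection acquired before study drug was available. PrEPX cannot avert such an infection, yet it counts in the post-period.

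The pre-period has carry-over of its own, but that does not cancel the problem. Infections carried into the pre-period arose at the same incidence as those within it. Infections carried into the post-period arose at the earlier, higher incidence if PrEP works. The measured decline is then too small. Restricting the count to newly acquired cases would shorten the lag but not remove it, because that definition itself allows up to 12 months.

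The aim is stated as a specific size of decline: 30% in GBM and 25% statewide. A programme that met its target exactly could be reported as having missed it.

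**Working it through.** **Inputs from the protocol (Sample size estimates).** 300 infections a year in Victoria, 225 of them in GBM; target 68 averted a year, or 30%. Check: 0.30 × 225 = 67.5, which rounds to the stated 68. Over 36 months, 3 × 225 = 675 GBM infections are expected without PrEP.

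**Assumptions (not in the protocol).** Stable incidence before opening; the full 30% fall from day 1; an exponential infection-to-diagnosis lag with mean m years, for m = 0.25, 0.5 and 1. Counts are treated as Poisson.

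**Step 1: carry-over share of expected post-period diagnoses.** Share = (m/3)(1 − exp(−3/m)).
- m = 0.25: 0.083, or 56 of 675
- m = 0.5: 0.166, or 112 of 675
- m = 1: 0.317, or 214 of 675

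**Step 2: decline seen over 36 v 36 months.** Observed = true decline × (1 − share).

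| Mean lag | True 30% (GBM) shows as | True 25% (statewide) shows as |
|---|---|---|
| 3 months | 27.5% | 22.9% |
| 6 months | 25.0% | 20.8% |
| 12 months | 20.5% | 17.1% |

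The statewide column applies the same shares to the 25% target.

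**Step 3: the same, leaving out the first 12 months.** Share in months 13 to 36 = (m/2)(exp(−1/m) − exp(−3/m)), giving 0.002, 0.033 and 0.159.
- GBM, true 30%: 29.9%, 29.0%, 25.2%
- Statewide, true 25%: 24.9%, 24.2%, 21.0%

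**Step 4: power to detect any decline.** Two Poisson counts over equal periods, two-sided 0.05: with p = 675/(675 + post count) and n the total, power = Φ{[(p − 0.5)√n − 1.96 × 0.5]/√(p(1 − p))}. At m = 0.5 the post count is 675 × 0.750 = 506 and power is over 99%. At m = 1 it is 675 × 0.795 = 537 and power is about 98%.

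**Step 5: does screening add to this?** Someone infected before opening and found positive at PrEPX screening is already in the Step 1 carry-over if they would otherwise have been diagnosed later in the window. The proportion of those undiagnosed at opening who would remain undiagnosed 36 months later is exp(−3/m): 0.25% at m = 0.5 and 5.0% at m = 1. Screening therefore mostly moves cases within the window and hardly changes its total.

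**Step 6: precision cost of the lagged contrast.** At m = 0.5, the standard error of the log rate ratio is √(1/675 + 1/506) = 0.0588 for 36 v 36 months. With the first 12 months left out, 450 × 0.710 = 319 post-period cases remain and it is √(1/675 + 1/319) = 0.068. The interval is about 15% wider on the log scale.

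**The case against.** The strongest reply is that the planned tests ask only whether there is a significant decline, and Step 4 shows that answer is safe for lags up to a year. The bias is also conservative, it rests on a lag the document does not give, and the Discussion already admits the proxy problem. All of this stands and limits the weight of the point. It does not remove it: the aim and the analysis section both name a 30% decline, and the windows are written out rather than left open.

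Three stronger readings are tempting, and the documents do not support them:
- **Screening diagnoses as a second, additional bias.** Step 5 shows that they largely overlap the carry-over. In waves two and three some may also reflect infection after 26 July 2016, so they are pre-enrolment rather than pre-PrEPX infections.
- **Gradual filling of places as a further loss of effect.** The 30% target was sized on 2,600 places, and Study funding adds 600 and 600 to reach 3,800. Roll-out is also part of what providing PrEP over 36 months means.
- **Greater dilution from stopping at the April 2018 PBS listing.** The plan sets 36 months and nowhere truncates there.

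A further reply is that the testing analysis need not be one-sided: its list of factors is open, rate ratios can exceed 1, and the ACCESS triangulation has no stated direction. That is fair, so the wording needs tightening rather than the analysis being absent. Finally, a lag chosen after enrolment began, in the direction that enlarges the effect, is open to criticism. That is why the lagged contrast should stand beside the stated one and not replace it.

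**Conclusion.** The point holds as a modest bias towards no effect in the size of the decline. For assumed mean lags of 3 to 6 months, a true and immediate 30% fall is reported as about 27.5% to 25.0%, a loss of 2.5 to 5 percentage points; at 12 months it is about 20.5%. The test for any decline is little affected.

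The direction follows from the windows and the diagnosis date, provided that PrEP lowers incidence. The size depends on the assumed lag, on stable prior incidence and on an immediate effect. A reader might infer that a true 30% fall could never be observed as 30%. That goes too far, because the count is subject to chance; the claim concerns the expected value.

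**What to change.** 1. Keep the 36 v 36 month contrast as stated.
2. Add a prespecified lagged contrast: leave out a fixed 12 months from 26 July 2016, compare the monthly notification rate after that with the monthly rate in the 36 months before opening, and report both contrasts together when judging the 30% and 25% targets. State that the lag reduces the dilution and comes close to removing it only when the lag is short.
3. Report HIV diagnoses made at PrEPX baseline screening as a separate count of pre-enrolment infections, taken from clinic or ACCESS data. Do not remove them from the state line list: it is non-identifiable, and removing cases from the post-period only would favour PrEP.
4. Word the testing analysis so that it examines rises as well as falls in notifications.

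Cost: mainly analysis wording, since diagnosis dates are already collected. The lagged contrast has 24 post-period months instead of 36 and an interval about 15% wider on the log scale. The report must say that the lag was added after enrolment began.

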### Ethics

Written informed consent is obtained from all study participants. The PrePX study was approved by the Alfred Health Human Research and Ethics Committee (HREC100/16) and registered on the Australian New Zealand Clinical Trials Registry (ACTRN12616001215415).

## Discussion

PrEP is a highly effective HIV prevention tool and may contribute to a meaningful decline in HIV transmission in Australia. PrEPX will deliver PrEP to 3800 individuals at high risk of HIV acquisition in Victoria. The PrEPX study will explore if the provision of PrEP contributes to a decline in HIV incidence, is associated with a change in participant behaviors, a change in the incidence of STIs and the capacity of clinics to provide PrEP on a large scale. This study design closely emulates a real world scenario and is likely to provide important data to guide PrEP implementation once PrEP become listed on the PBS in Australia.

The design of PrEPX, is a key strength of the study. Community groups have representatives as co-investigators on the study and provide information to their communities and to the study team, contributing to iterative refinement of the study. Consultation with clinics allowed clinics to plan for study enrolment and to provide feedback to the study team when they reached capacity. Electronic data collection, including study enrolment, behavioral data and test data collection decrease the clinical trial burden placed on clinics and with the exception of enrolment, utilize the existing ACCESS sentinel surveillance system at most clinic sites. This design provides long term, high quality clinical and behavioral data among GBM testing for HIV and STIs, allowing for population level estimates of the impact of PrEP while maintaining standard practice at participating sites. At the drug dispensing level the involvement of community pharmacies and the requirement for participants to pay for study drug in accordance with government approved dispensing fees following PBS listing, will provide important information on affordability in a real world setting and will further allow trial participants to better plan for ongoing costs of taking PrEP once approved on the PBS.

There are a number of limitations in this study. While efforts were made to emulate real world setting the exclusion criteria, limited number of study spaces, and compensation of clinics for each enrollee introduce aspects to the study that will not be present when PrEP is listed on the PBS. Also, while there is significant data collected in this study, the restriction of behavioral and test data is only collected from sites participating in the ACCESS surveillance system, however we anticipate that the vast majority of clients will be enrolled at these sites. Finally, HIV diagnoses are being used as a proxy for HIV incidence and may not accurately reflect incidence. However, we aim to triangulate HIV notification in Victoria, with diagnoses and testing at ACCESS surveillance sites to improve estimates of the impact of PrEPX.

PrEPX will provide important evidence on an approach that emulates the real world when implementing PrEP on a large scale at a time when much of the world is transitioning to the use of this new HIV prevention tool. The PrEPX study design will allow researchers to determine if provision of PrEP to people at risk of HIV in Victoria reduces HIV transmission. In addition, it will provide important information on behavioral change and STI rates, attitudes toward PrEP, ancillary health benefits of quarterly clinical visits and the health service requirements for providing PrEP on a large scale. PrEPX will deliver implementation and population level results that will be transferrable to other Australian jurisdictions and international settings.
